## Abstract

**Background:**

Homecare re-ablement services have been developed by local authorities in England in response to the government agenda for health and social care. These services aim to optimize users’ independence and ability to cope at home, and reduce the need for ongoing health and social care services. However, there is currently limited evidence and guidance regarding the optimum configuration and delivery of re-ablement services. In particular, the impact of occupational therapy input on service user outcomes has been highlighted as a specific research priority.

**Methods/Design:**

This feasibility randomized controlled trial (RCT) will recruit 50 people from one local authority led homecare re-ablement service in England. Those who provide informed consent will be randomized to receive either usual homecare re-ablement (without routine occupational therapy input) or usual homecare re-ablement plus an enhanced program targeted at activities of daily living (ADL), delivered by an occupational therapist. The primary aim of this study is to assess the feasibility of conducting a further, powered study. The participant outcomes assessed will be independence in personal and extended ADL, health and social care-related quality of life, number of care support hours, falls, acute and residential admissions and use of health and social care services. These will be assessed at two weeks, three months and six months post-discharge from the re-ablement service.

**Discussion:**

To our knowledge, this is the first RCT of occupational therapy in homecare re-ablement services. The results of this study will lay the foundations for a further powered study. The findings will be relevant to researchers, clinicians, commissioners and users of adult social care services.

**Trial registration:**

Current Controlled Trials registration number: ISRCTN21710246 (registered on 31March 2014)

## Background

In England, the Department of Health has highlighted its commitment to re-ablement services in the white paper *Caring for Our Future: Reforming Care and Support*
[1]
*.* This document outlines the government’s vision that the provision of these services should support people to remain living independently in their homes after a crisis event. It has been further highlighted that the National Health Service (NHS) and local authorities should work jointly to provide support for people leaving hospital, or recovering from illness or injury, in order to improve outcomes for users (such as their ability to manage personal care independently), and to deliver cost savings for both organizations [2]. However, there is limited guidance regarding the optimum configuration and skill mix of re-ablement teams [3], and the role and remit of occupational therapists in these services has been highlighted as a particular research priority [4].

### ‘Homecare’ and ‘homecare re-ablement services’

Within adult social care services in the United Kingdom, ‘homecare’ is the term used to describe a type of community service in which a care worker visits the person at home to give assistance with everyday activities such as washing, dressing and meal preparation. Homecare is usually delivered by care workers who may or may not have a vocational care qualification, and does not usually involve qualified healthcare professionals. Homecare may be provided on a short- or long-term basis, depending on the needs of each individual service user [5].

In a homecare re-ablement service, users receive homecare but are supported to increase their ability to manage tasks independently, in order to reduce the amount of homecare they will require in the longer term [6]. Increasingly, such services have been developed by local authorities in England to work with people who are newly referred to social care services as needing homecare support [3, 7]. This could mean adults having difficulties managing independently at home, for example, people leaving hospital, recovering from illness or injury or experiencing a new deterioration of a long-term condition. Homecare re-ablement teams usually work with users for up to six weeks, with some flexibility to extend this in certain circumstances [8]. After six weeks, those users who require ongoing help are referred to a traditional homecare team for longer-term support. Internationally, comparable services are referred to as ‘restorative homecare’ [9–12], and may operate within similar parameters to homecare re-ablement.

Homecare re-ablement differs from community rehabilitation in that services adopt a social model of recovery rather than a medical model [13]; there is also a specific focus on reducing the need for paid homecare support. Whilst some re-ablement teams have significant therapy input, others are managed and staffed by social care workers who may have received training in re-ablement philosophies and approaches [6].

### Homecare re-ablement and occupational therapy

Eligibility for homecare re-ablement services is predominantly based around the need for assistance with personal care activities in the home environment. Increasing independence in activities of daily living (ADL), and modifying the home environment to increase independence and reduce risks, are among the core skills of the occupational therapist [14]. These skills are clearly compatible with homecare re-ablement service aims and this has been identified by the United Kingdom College of Occupational Therapists (COT). In a position statement published in 2010, the COT highlighted the similarities between the philosophy of occupational therapy and re-ablement approaches, and argued that successful outcomes for service users and demonstrable cost benefit for local authorities depended upon the involvement of occupational therapists [15].

Previous studies have suggested that targeted occupational therapy assessment and intervention can improve people’s ability to manage ADL independently in a variety of different contexts [16–20]. However, specific research is required within re-ablement services in order to test the effectiveness with this particular service user group, evaluate the impact on users’ ability to manage independently and assess the effects on the cost of ongoing health and social care services.

### Why is this study needed?

Homecare re-ablement services are currently high on the policy agenda, forming part of a national strategy to reduce the number of people requiring ongoing care [1]. The primary goal of these services is to assist users to regain lost skills and abilities [21], with an emphasis on those skills pertaining to personal care and meal preparation. Given the specialist skills of occupational therapists in this area, it may seem logical that occupational therapists should be involved in these services; however, the extent and nature of their input varies nationally and internationally. Services have developed sporadically across England, in line with regional variations in health and social care commissioning policies, and thus not all teams directly incorporate the skills of occupational therapists [22].

A controlled before and after study published in 2010 compared five local authority sites with re-ablement services with traditional homecare services [8]. This study reported that 29% of the users who received the re-ablement service had input from an occupational therapist during the re-ablement episode. However, the study authors reported that it was not possible to determine whether the outcomes were better for users who received occupational therapy input compared to those who did not [8]. Thus, there is a requirement for further research which investigates outcomes for service users who receive occupational therapy. Research should also examine whether there are cost savings for local authorities associated with the inclusion of such a targeted occupational therapy intervention in homecare re-ablement teams.

As a precursor to this randomized controlled trial (RCT), a systematic review was conducted. The protocol was published prospectively [23] and the manuscript is currently in preparation. No previous RCTs of occupational therapy interventions for users of homecare re-ablement or restorative homecare services were identified in the systematic review.

## Methods/Design

### Research aim and objectives

Our overall aim is to conduct an RCT to determine whether an occupational therapy intervention can improve the ability of homecare re-ablement service users to carry out ADL independently. This feasibility RCT will enable us to ascertain the viability of conducting a definitive appropriately powered study. It will also allow us to conduct preparatory health economic evaluation work.

### Study setting

This single-centre feasibility study will be conducted within one city council homecare re-ablement service in England. The service is divided into six geographical sub-teams. This RCT will be conducted within one sub-team, which currently does not have routine input from an occupational therapist.

### Participants

The re-ablement service accepts referrals from any adult aged over 18 years, living in the community, with a need for homecare support, except those with a diagnosis of dementia who have a specialist dementia homecare service within the area. All users of the homecare re-ablement service within the selected sub-team will be screened for eligibility. Inclusion criterion for the trial is the ability to provide informed written consent. Exclusion criteria are: inability to speak English, on an end-of-life care pathway, requiring assistance from two or more people to transfer or receiving input from a community rehabilitation team.

### Intervention and comparator

Participants will be randomized to either usual homecare re-ablement (control group) or the occupational therapy intervention (intervention group). Those randomized to the control group will receive the usual routine care provided by the homecare re-ablement service, that is, a six-week period of homecare re-ablement provided by re-ablement workers (paid care workers), under the direction of a re-ablement care team leader. This does not involve input from qualified health professionals. Therefore, the control group will not routinely receive specialist ADL assessment and intervention, or routinely access community equipment or minor adaptations provided by an occupational therapist as part of their re-ablement package. This is current practice within the sub-team at the trial site. However, if service users in the control group are identified as requiring specific occupational therapy input, they will be referred to the mainstream community occupational therapy team (waiting time currently exceeds the six-week re-ablement period). Referrals to occupational therapy are not routinely made.

Those randomized to the intervention group will receive all routine homecare re-ablement services but, in addition, will receive an enhanced program targeted at ADL, delivered by an occupational therapist. The aim of the enhanced program will be to maximize independence in ADL activities including (but not limited to): washing, dressing, bathing and showering, feeding, indoor mobility, transfers, stair mobility, toileting, meal preparation and kitchen activities, outdoor mobility and community access (as appropriate to individual participants).

Following the re-ablement service referral, a systematic assessment will be completed by an occupational therapist within five working days. This will identify difficulties the service user may have with ADL due to physical impairments, psychological difficulties or a combination of both. The assessment will be used as a basis to set one or more ADL-related goals for the re-ablement episode. A program will then be agreed with the participant, which will be tailored to the needs of each individual, but will include: practicing activities, and/or a graded process of re-learning and building the skills to manage ADL independently; equipment provision and environmental or activity modification. A case management approach will be adopted by the occupational therapist involving a minimum of weekly reviews and the coordination of the re-ablement episode and other services. Advice and information will also be provided to family members or carers.

The intervention will utilize the occupational therapist’s core skills in activity analysis, where an activity is broken down into its distinct component parts in order to identify the specific element(s) of the task which the individual is unable to perform [24]. The occupational therapist will combine their medical knowledge of prognosis with their assessment of functional ability in order to select an appropriate approach for the re-ablement episode (for example a compensatory or a bio-mechanical approach).

Timely provision of community equipment and/or minor adaptations (such as grab rails, half-steps or threshold removal or replacements) will form a core component of this intervention. These will be prescribed by the occupational therapist and provided by the Community Equipment Service for the local area. The occupational therapist will complete an ongoing review of the use of equipment in order to assess whether the continued use is warranted or no longer required. The enhanced input will continue for the duration of the re-ablement episode (up to six weeks), and will cease when the service user is discharged from the re-ablement service.

### Cost evaluation

As part of the cost evaluation, a record will be kept of the number of times the occupational therapist visited each service user in the intervention group, the amount of time spent per visit and a log of what was carried out on each visit (in the form of a coded checklist). In addition, a record will be kept of the cost of equipment and minor adaptation services provided. Participants in both groups will report their use of health and social care services during the intervention and follow-up period.

### Concomitant treatments

There are no known issues with the treatment and concomitant treatments. However, participants who are receiving input from specialist community rehabilitation services (such as intermediate care or community stroke team) will be excluded. Information will be kept on the participant’s use of other community rehabilitation services (such as private therapists) and will be reviewed as part of the assessment of feasibility.

### Compliance

Compliance with the treatment intervention will be monitored by the occupational therapist delivering the intervention. This will be defined as participation in treatment visits and willingness to continue with treatment (further visits).

### Outcomes

The primary trial outcome will be a determination of the feasibility of conducting a larger, appropriately powered trial. The assessment of feasibility will be a composite measure of recruitment, retention, acceptability and the viability of delivering the intervention. Key aspects to be addressed are: whether the eligibility criteria are realistic, whether service users are willing to be randomized, the dropout rate, the content and scheduling of the occupational therapy treatment visits, the acceptability of the occupational therapy intervention, the most suitable primary outcome measure for the main study and the feasibility of the cost data collection.

The participant outcomes to be assessed will be: personal and extended ADL, health and social care-related quality of life, number of care support hours, health and social care service usage and carer strain. The measures are: Barthel Index (BI), Nottingham Extended Activities of Daily Living (NEADL), Short-Form 36 (SF-36), Adult Social Care Outcomes Toolkit (ASCOT), EQ-5D and Caregiver Strain Index (CSI). Additionally, information will be collected on: number of homecare hours, falls, admissions (to acute and residential services) and use of health and community services. The Mini-Mental State Examination will be completed at the baseline time point in order to provide a description of the sample. The timeline and proposed flow of participants through the study are shown in Figure 1.

**Figure 1 Fig1:**
[figure not shown]
**Flow of participants through the study.**

Acceptability of treatment will be ascertained using a purposely designed questionnaire, which will be left with all participants in the intervention group, after the occupational therapy input has ended. This questionnaire will include questions on their views of the occupational therapy intervention and will cover its content, frequency, delivery, timing and intensity. Additionally, interviews will be completed with up to five participants who received the treatment intervention, in order to explore their views and experiences of the intervention. These post-intervention interviewees will be purposively selected for a variety of features including: underlying diagnostic condition, prior experience of receiving occupational therapy and homecare, age, those who live alone and those who live with support.

### Sample size and recruitment strategy

For a feasibility study, no formal sample size calculation is required. The aim is to recruit 50 participants (25 in each arm of the trial) to test the randomization process and the acceptability of the intervention. The trial will recruit for eight months. Current data from the trial site suggests that approximately three service users per week will be eligible. A maximum of 10 participants will be recruited per calendar month. Potential participants will be approached in the order in which they are referred to the re-ablement service. If 10 participants consent during a calendar month, recruitment will cease until the first new referral of the next calendar month. If the maximum of 50 participants are recruited before the end of the eight-month period, recruitment will cease.

Participants will be enrolled into the study by the investigator. The process for obtaining informed consent will be in accordance with the Research Ethics Committee (REC) guidance, and Good Clinical Practice (GCP) and any other regulatory requirements that might be introduced. The investigator and the participant shall both sign and date the informed consent form before the person can participate in the study. Randomization will be generated online by the Nottingham Clinical Trials Unit (NCTU) using a web-based randomization program. Participants will be individually randomized in random varying block sizes (sized in order to deliver the clinical intervention appropriately). Randomization will be at a ratio of 1:1 (treatment-to-control). Only the NCTU will have access to the allocation sequence. Baseline assessments will be completed prior to randomization. Follow-up assessment visits will be completed by a research assistant who is masked to the treatment allocation. It is possible that participants may reveal their treatment allocation to this assessor, and any instances of this will be recorded as part of the assessment of feasibility.

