### Data collection, management and analysis

Data will be collected in the participants’ homes on a paper case report form (CRF) and will subsequently be entered onto a secure password-protected electronic database. Outcome data will be entered by the research assistant who collected the data (and thus will be entered blind to treatment allocation). Each participant will be assigned a trial identity code number, allocated at randomization, for use on CRFs, other trial documents and the electronic database. The documents and database will also use their initials and date of birth.

CRFs will be treated as confidential documents and held securely in accordance with regulations. The investigator will make a separate confidential record of the participant’s name, date of birth, local social care number and participant trial number to permit identification of all participants enrolled in the trial, in accordance with regulatory requirements, and for follow-up assessments as required. Access to CRFs shall be restricted to those personnel approved by the chief investigator.

When data collection is complete, a data quality check will be conducted in duplicate by two researchers and a 10% sample of the database will be checked against the original paper CRF. Steps will be taken to minimize missing data via personal contacts throughout the study period from the investigator, and every attempt will be made to locate participants for follow-up assessment. Outcome data will be collected in person by a research assistant to minimize the amount of missing data. For each outcome measure used where data is missing, an imputed average will be used for items where less than 10% of the overall measure is missing. Where more than 10% of a measure is missing, the entire measure will be coded as missing.

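### Assessor masking is likely to be lost for some participants through cues in the home, and the planned log counts only what participants reveal

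*Protocol article*

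**What the plan says.** All of the following is in the Protocol article.

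- **Masking** (Sample size and recruitment strategy): "Follow-up assessment visits will be completed by a research assistant who is masked to the treatment allocation". The next sentence names one way this can fail: "It is possible that participants may reveal their treatment allocation to this assessor, and any instances of this will be recorded". It makes those records part of the feasibility assessment.
- **Place and person** (Data collection, management and analysis): "Data will be collected in the participants’ homes on a paper case report form (CRF"), and "Outcome data will be collected in person by a research assistant to minimize the amount of missing data".
- **Data entry** (same section): "Outcome data will be entered by the research assistant who collected the data (and thus will be entered blind to treatment allocation").
- **Equipment** (Intervention and comparator): the intervention has as a central part "Timely provision of community equipment and/or minor adaptations (such as grab rails, half-steps or threshold removal or replacements"). Controls do not routinely get such items from an occupational therapist within their re-ablement package. They can be referred to the mainstream therapy team, whose waiting time is longer than the six-week episode.
- **Service use** (Outcomes): the information to be collected includes "falls, admissions (to acute and residential services) and use of health and community services". Cost evaluation adds: "Participants in both groups will report their use of health and social care services during the intervention and follow-up period".

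**The concern.** The assessor is declared masked but works where the intervention may leave visible traces. The assessor probably also asks about a period in which one arm had at least weekly reviews by an occupational therapist. The plan treats participant disclosure as the only way masking can fail, and then describes data entry as blind without qualification.

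Two things are at stake. First, how well masking holds is one of the trial's own feasibility findings. A log that covers one route only would make the scheme look better than it is, and that scheme could be carried into the definitive trial. Second, an assessor who believes they know the arm may score function and quality of life differently. The differences between arms at two weeks, three months and six months are meant to inform the treatment effect estimate and the sample size of the later trial.

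**Working it through.** The plan gives no figure to reproduce, so the check sets its statements side by side.

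**1. Is data entry blind?** The data-entry sentence infers blindness from the fact that the person entering the data also collected them. That inference needs the collector to be still masked after the visit. The masking paragraph concedes that a participant may reveal the allocation to this same assessor. Where that happens, the data from that visit are entered by someone who knows the arm. The two statements are inconsistent as written, whatever the rate of disclosure.

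**2. Can the home reveal the arm?** Follow-up is in the home. Rails, half-steps and threshold changes are fixed and visible. They are central to one arm and not routine, through an occupational therapist, in the other. For a participant with a full six-week episode, the first follow-up falls about 6 + 2 = 8 weeks after the start. A control referred to the mainstream team waits more than six weeks, so the contrast between arms is probably sharpest at that visit and weaker at three and six months. Seeing an item involves no disclosure by the participant, so the log as described has no place for it.

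**3. Can the service-use questions reveal the arm?** Service use is a listed outcome, is reported by participants, covers the intervention period, and outcome data are collected in person by a research assistant. The natural reading is that the masked assistant asks. An answer that mentions the therapist's visits then points to the intervention arm. The article does not say who asks, in what order, or whether occupational therapy is itemised.

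**4. What does the log measure?** Let D be the participants who reveal their allocation and S those whose allocation the assessor infers without being told. Unmasking is D + S, and the log reports D. The shortfall is S, which is zero or more, so the log can only understate. The document gives neither D nor S.

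**5. What does the shortfall touch?** It touches the masking part of the feasibility assessment. If scoring is influenced, it also touches the arm differences in outcomes. It does not touch the screening and recruitment log, loss to follow-up or the acceptability questionnaire, on which the main feasibility analysis rests.

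**The case against.** The strongest reply is that the plan has already seen the risk: it admits masking may fail, records the failures and counts them in the feasibility assessment. The main endpoint does not depend on the assessor's scores. The case report form and full protocol are not shown, and question order and wording belong there. This stands as far as it goes, but it does not extend the log to what the assessor sees, and it does not reconcile the data-entry sentence.

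A reader might infer several stronger things that the document does not support:

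- **That the assessor will be unmasked.** No unmasking or equipment rate is given. The program is tailored to the individual, so some intervention participants may have no visible item. A rail is a cue, not proof.
- **That equipment appears in one arm only.** Controls are said only not to get it routinely from an occupational therapist within re-ablement. Some may own equipment already or receive community therapy later.
- **That all 25 intervention participants could be identified before the later visits.** That number is simply the arm size. It assumes full recruitment, no dropout and complete disclosure at the first visit.
- **That one assessor sees each participant at every visit.** The article does not say so.
- **That the log misses answers to service-use questions.** A participant who describes the therapist's visits has arguably revealed the allocation, and nothing limits the log to spontaneous remarks. The clear gap is visual cues and the assessor's own inference.

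**Conclusion.** The point holds in a limited form. Masking is likely to be compromised for some participants. The planned record omits unmasking by sight or inference, so it would understate the problem. The unqualified statement that data are entered blind conflicts with the plan's own concession.

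The size cannot be computed from the document; only the direction of the error in the log is certain. The conflict over data entry rests on the text alone. The equipment route assumes that some intervention participants have visible items at follow-up. The service-use route assumes that the masked assistant asks those questions, which is the natural reading but is not stated. This is a worthwhile, inexpensive improvement and does not threaten the main feasibility endpoint.

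**What to change.** 1. At each follow-up visit, complete the ADL and quality-of-life scales before any service-use questions.
2. Then have the assessor record any unmasking, whatever its source (participant, equipment seen, service-use answer, other), and a guess of the allocation.
3. Report both by arm and visit. With 1:1 allocation, guessing at random is right half the time, so the guesses should be read against one half and alongside the stated source.
4. Qualify the data-entry sentence: entry is blind only where the assessor has remained masked.

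The cost is one or two extra form items per visit, over at most 50 × 3 = 150 visits. Treatment, sample size and visit schedule are unchanged. Two limits remain. Asking about service use last does not hide equipment, and it protects scores only at that visit if the same assistant returns. The record in step 2 makes both visible in the results.

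Moving service use to a self-completed form or to the investigator would remove that cue more fully, but it is a trade-off. A self-completed form works against the plan's reason for in-person collection, which is to limit missing data. The article nowhere describes the investigator as masked. That move is not needed to correct the point.
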